### Safety evaluation

Adverse events (AEs) concerning clinical symptoms and signs as well as laboratory tests will be documented. Every AE will be recorded in detail, and prompt, proper treatment will be given by researchers and therapists at each center. If a serious adverse event (SAE) presents, a decision on whether the participant needs to be withdrawn from the study will be made by the principal investigator and ethics committee. The causality and relationship between AEs/SAEs and the study drug will also be analyzed and evaluated on the basis of standard operation procedures (SOPs) of the CFDA, which define causality and relationship as clearly related, probable, possible, doubtful, and clearly not. If an SAE occurs, the investigator must record it in detail on the SAE form, and it should be reported to the principal investigator, the CFDA, ethics committee, and the sponsor within 24 hours. A statistician will analyze the frequency and proportion of AEs/SAEs. Continuous care will be available until subjects who suffer harm from the participation recover, and proper compensation will also be given.

Primary vital signs, physical examinations, and some laboratory tests will be performed both before and after treatment for safety assessment. Primary vital signs include body temperature, blood pressure, heart rate, and respiration rate. Laboratory tests include routine blood, urine, and stool analysis, liver function test (ALT, AST, alkaline phosphatase (ALP), serum total bilirubin (STB), and gamma-glutamyl transpeptidase (γ-GT)), renal function test (serum creatinine, microalbuminuria, and serum cystatin C), and electrocardiogram. Also, before treatment, subjects who are suspected to have a lower respiratory tract infection need have a chest X-ray, and female patients with the potential to become pregnant must take a urine pregnancy test.

### Efficacy assessment

#### Primary outcome

The primary outcome is the time to all symptoms’ clearance, which is defined as the length from study enrollment to the time when the symptoms completely disappear. Each participant will be instructed to record any change in symptoms in their patient diary.

#### Secondary outcomes

Secondary outcomes include time to primary symptoms and each secondary symptom disappearance, time to fever relief, time to fever clearance, and change in TCM symptom and sign scores.

Time to fever relief is defined as the time from the first dosing to time when the body temperature drops by at least 0.5 °C. Time to fever clearance is defined as the time from the first dose administration to the time when the body temperature drops below 37.3 °C and lasts for 24 hours.

In this study, all patients will be required to record their body temperature in the patient diary every 2 hours within the first 12 hours and every 4 hours during the following 12 hours. After that, if the temperature is ≥37.3 °C, it should be recorded four times at a fixed time every day, and if the temperature is lower than 37.3 °C, then there is no need to record it.

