### Concomitant treatments and forbidden drugs

Patients will be allowed to continue using medications for underlying conditions, such as hypertension or diabetes. The name, dosage, and duration of any concomitant medication must be recorded carefully in the case report form (CRF). If the body temperature of a participant rises to higher than 39.0 °C for longer than 2 hours or becomes ≥39.5 °C, physical cooling and/or paracetamol can be used to kill the fever. During the study period, any other Western or Chinese therapy or medication that may affect the study results is prohibited. Once forbidden drugs are used, the patient will be withdrawn from the study.

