### Data management and statistical analysis

The Drug Clinical Research Center of Shanghai University of TCM is in charge of data statistical analysis. The data entry will be performed by two independent data administrators using the software EpiData 3.1 based on the CRFs, which should have been checked and reviewed for accuracy and consistency by the clinical research associate (CRA) and investigators. Finally, the database will be locked and analyzed under the agreement and confirmed review of the sponsor, principal investigator, and statistician.

The full analysis set (FAS), in which patients should be dosed with LJGMG or placebo at least once with clinical observation record in the study, is the primary analysis set according to the intention-to-treat (ITT) principle using the last observation carried forward (LOCF) approach for missing values. All subjects without any major protocol deviations will be included in the per-protocol set (PPS). An efficacy assessment will be carried out using the FAS and PPS. A safety evaluation will be conducted for subjects who have experienced at least one study visit and have safety data, which is defined as the safety set (SS).

All continuous and normally distributed data are presented as mean ± standard deviation, and median with range for non-normal data. Categorical data are summarized by frequency counts and percentages. Baseline balance among groups will be conducted by performing a chi-squared test or an analysis of variance (ANOVA). Time to all symptoms’ clearance, time to primary symptoms and each secondary symptom disappearance, time to fever relief, and time to fever clearance will be estimated and compared by the log-rank test. A Kaplan-Meier survival curve will be constructed, and the median time will be provided separately for each group with a two-sided 95% confidence interval. Comparisons among groups of TCM symptom and sign scores will be conducted using ANOVA and the Bonferroni method. All data will be processed by a professional statistician using SAS 9.2 software (SAS Institute, Cary, NC, USA); a two-sided *P* value of <0.05 is considered to be statistically significant.

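### As worded, a temperature fall after permitted paracetamol or physical cooling can count as fever relief and, if sustained, as fever clearance, which may pull both secondary comparisons toward no difference

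*Protocol article*

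**What the plan says.** **Definitions (Protocol article, Secondary outcomes).** "Time to fever relief is defined as the time from the first dosing to time when the body temperature drops" by at least 0.5 °C. Fever clearance runs from the first dose to "the time when the body temperature drops below 37.3 °C and lasts for 24 hours". Neither refers to rescue. The relief definition does not say which temperature the 0.5 °C is measured from.

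**Rescue (Concomitant treatments and forbidden drugs).** The trigger is "If the body temperature of a participant rises to higher than 39.0 °C for longer than 2 hours or becomes ≥39.5 °C"; then "physical cooling and/or paracetamol can be used to kill the fever". Next, "any other Western or Chinese therapy or medication that may affect the study results is prohibited", and use of forbidden drugs leads to withdrawal. Because the prohibition covers other therapies, this section does not withdraw a patient for permitted rescue.

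**Withdrawal criteria.** Under worsening condition, this section lists a temperature that rises above 39.0 °C. Whether the 48-hour limit at the end of that item applies to it is unclear.

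**Analysis (Data management and statistical analysis).** The primary set is the FAS: patients dosed at least once who have an observation record, "using the last observation carried forward (LOCF) approach for missing values". For the fever endpoints, "time to fever relief, and time to fever clearance will be estimated and compared by the log-rank test". The article gives no rule for temperatures after rescue or after withdrawal.

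**The concern.** A time-to-event endpoint for fever should measure how quickly the assigned treatment brings the temperature down. Here the event depends on the size of the fall, and for clearance on its duration, but not on its cause. A fall produced by an antipyretic or by physical cooling can therefore be credited to the randomised arm.

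The problem is not random noise, because the trigger for rescue is the quantity being measured. Patients enter below 39.0 °C (Exclusion criteria), so a rescued patient has got worse since entry. If the study drug lowers fever, rescue should concentrate on placebo and perhaps the lower doses. Patients who would have had late events are then given early ones. The arms are drawn together, and the dose-efficacy relationship that the trial hopes to find (Background) is flattened on these endpoints.

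**Working it through.** **1. The plan's own figure.** The only stated sample size concerns the primary outcome: difference 2 days, SD 3, two-sided α 0.05, power 90%. n = 2 × (1.96 + 1.2816)² × 3² / 2² = 47.3, rounded up to 48; 48 / (1 − 0.20) = 60. Both figures reproduce, and this point does not alter them. The 60 per arm is used below.

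**2. Can a fall after rescue meet the definition of relief?** This depends in part on the unstated reference temperature.
- First dose 38.6 °C, rescue at 39.2 °C, then 38.0 °C: the fall is 0.6 °C from first dose and 1.2 °C from the peak. It counts either way.
- First dose 38.2 °C, rescue at 39.2 °C: measured from first dose, the temperature must reach 37.7 °C, a fall of 1.5 °C from the peak. Measured from the peak, 38.7 °C is enough.

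Readings are two-hourly for the first 12 hours and relief has no minimum duration, so a brief dip is enough.

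**3. Clearance.** A transient dip does not qualify, because 24 hours below 37.3 °C are needed. However, after the first 24 hours readings below 37.3 °C need not be recorded. Whether a fall after rescue really lasted would be hard to verify from the diary.

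**4. Illustrative size for relief.** The documents give no rescue rate, no rescue timing and no median time to relief, so every input except 60 per arm and the 192-hour horizon (8 days × 24) is an assumption.

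*Set-up A:* one active arm against placebo; exponential times with medians of 20 h (placebo) and 11 h (active), rounded to two-hourly readings; rescue at 4–20 h among patients in the slower half; fall within 2 h of rescue; 1,500 to 3,000 runs per scenario where the number is given. Log-rank power without any rescue effect is about 89%. Two figures in a cell come from separate runs, and a dash means no figure is available.

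| Rescue, placebo vs active | Falls counted | Censored at rescue | Event not reached |
|---|---|---|---|
| 2% vs 1% | 88% | – | 84% |
| 3% vs 3% | 87% | – | 70% |
| 5% vs 2% | 82% | – | 83% |
| 5% vs 5% | 85–86% | 87% | 63–64% |
| 10% vs 3% | 73–74% | 85% | 89% |
| 15% vs 5% | 59–61% | 80% | 89% |

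Loss when falls are counted: 89 − 87 = 2 points at 3% vs 3%; 89 − 73 = 16 at 10% vs 3%; 89 − 59 = 30 at 15% vs 5%. At 2% vs 1% the loss is 1 point, which is within simulation error. The gap of 2 points or less between censoring and counting at 5% vs 5% should also not be over-read.

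*Set-up B:* medians 24 h and 13 h; rescue at 4–16 h, unrelated to prognosis; event 2 h later; 4,000 runs. Power falls from 91% to 87% (5% vs 2%), 84% (10% vs 5%), 73% (20% vs 10%) and 53% (30% vs 10%). The rate ratio falls from 1.85 to 1.80, 1.76, 1.68 and 1.53. The last scenario, a loss of 91 − 53 = 38 points, is the most extreme assumed.

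**The case against.** **An open handling rule, not an error.** How rescue is scored is often left to an analysis plan, and none is shown. Counting events regardless of rescue is also a recognised treatment-policy approach, compatible with the intention-to-treat principle that the article invokes. This has weight: the article nowhere says that readings after rescue count. But the definitions are stated without qualification, and applied as written they take in such falls. Handling set elsewhere would have to override them.

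**Rescued patients may be withdrawn.** A temperature above 39.0 °C appears under Withdrawal criteria, so most patients who qualify for rescue may also qualify for withdrawal. A reader might infer that rescue in the worse-off arm is certainly scored as treatment success. The documents do not support this, since the article does not settle whether later temperatures are collected or analysed. Nor does the withdrawal criterion remove the problem: withdrawal does not take a patient out of the FAS, and nothing says that later readings stop counting.

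**Not any fall counts.** A reader might also infer that every drop after rescue is an event, equally for both endpoints. The thresholds rule this out. Relief is the more exposed endpoint, and the simulation covers relief only.

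**The size is assumed.** This stands. Entry below 39.0 °C gives no support for a high rescue rate, and at the lowest rates little is lost.

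**Treating rescued patients as not reaching the event can do harm.** This stands too. At 5% vs 5% rescue it gives about 63–64% power, against 85–86% with falls counted. It should not be the main analysis.

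**Conclusion.** The point holds in a limited form. The definitions as worded allow a fall after permitted rescue to end the relief clock and, if it is sustained, the clearance clock. If placebo patients are rescued more often, the bias is toward no difference. It hides an effect and does not create false efficacy.

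The documents do not allow the size to be calculated. For relief, assumed rescue rates of 3% to 15% on placebo cost about 2 to about 30 points of power; rates beyond that would cost more. These figures rest on exponential times, assumed medians, and every modelled rescue producing a counted fall within about 2 hours. Censoring at rescue was no worse than counting the falls in each scenario where the two were compared.

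Both endpoints are secondary and the sample size is untouched, so this is a change that should be made but not one on which the trial stands or falls.

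**What to change.** 1. Add one sentence to each fever definition: readings taken after physical cooling or paracetamol do not count as events. State the reference temperature for the 0.5 °C fall.
2. In the main analysis of both endpoints, censor at the time of rescue. Report two sensitivity analyses: rescued patients carried as event not reached to the end of follow-up, and all falls counted regardless of rescue.
3. Record the clock time of each rescue, including physical cooling. The article requires name, dosage and duration of concomitant medication; it does not name physical cooling or the time of rescue.
4. Reconcile Withdrawal criteria with Concomitant treatments and forbidden drugs on whether a patient above 39.0 °C is withdrawn, or rescued and kept in. State whether later temperatures enter the analysis.

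**Cost.** A few sentences, one data field and two extra analyses. Rescued patients contribute no event to the main analysis. Censoring at rescue is informative, because rescue marks a worse course, which is why the two sensitivity analyses are needed. The article describes the trial as still recruiting, so on that status the change can be made before unblinding.

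### Time to fever relief counts any unconfirmed 0.5 °C fall, and a patient entering at 37.3–37.6 °C can meet fever clearance yet be censored as not relieved

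*Protocol article*

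**What the plan says.** All of the following is in the protocol article.

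- **Fever relief** (Secondary outcomes). "Time to fever relief is defined as the time from the first dosing" until "the body temperature drops by at least 0.5" °C. No duration, confirming reading or alternative criterion is given, and the reading from which the fall is measured is not named.
- **Fever clearance** (same paragraph). The event occurs when "the body temperature drops below 37.3" °C "and lasts for 24 hours". This definition does carry a persistence condition.
- **Diary readings** (same section). Temperature is recorded "every 2 hours within the first 12 hours and every 4 hours during the following 12 hours". After that it is recorded four times a day while at or above 37.3 °C; below that level, "then there is no need to record it".
- **Who can enter.** Fever is one of the primary symptoms required for the diagnosis (Diagnostic criteria, Table 2). The mildest fever grade is 37.3–37.9 °C (Table 4). The Exclusion criteria set only an upper limit, 39.0 °C.
- **Analysis** (Data management and statistical analysis). Relief and clearance are each compared by the log-rank test with Kaplan-Meier curves. No rule links the two.

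**The concern.** There are two separate weaknesses in the one definition.

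First, the event is the earliest of many readings to cross a threshold, and one reading is enough. Frequent readings give reading error many chances to produce an event. In a patient whose fever has not truly fallen, such events arise without regard to treatment, so they pull the arms together and weaken the relief comparison.

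Second, relief is a relative fall and clearance is an absolute level. For the lowest eligible fevers, 0.5 °C is more than the distance to the clearance line. A patient can lose the fever for 24 hours and still count as not relieved, so the milder outcome is missed while the stronger one is met. The diary rule adds to this: once a patient is below 37.3 °C after the first day, a later further fall may never be recorded.

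The relief outcome helps to describe fever response across three doses and placebo, so its events should mean what their name says.

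**Working it through.** **The plan's own figure.** The plan gives no figure for fever relief. Its sample size concerns the primary outcome only and reproduces: 2 × (1.960 + 1.282)² × 3² / 2² = 47.3, so 48 per group, and 48 / 0.8 = 60. The present point does not depend on it.

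**Step 1: number of readings.** Every 2 hours for 12 hours gives 12/2 = 6. Every 4 hours for the next 12 hours gives 12/4 = 3. The total is 9 readings after the first dose.

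**Step 2: false relief when nothing changes.** Hold true temperature constant. Give the pre-dose reading and each of the nine later readings independent normal error with standard deviation s. The protocol states no s, so it is an assumption and is ranged.

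For one later reading, P(fall ≥ 0.5) = 1 − Φ(0.5 / (s√2)). At s = 0.20 °C this is 1 − Φ(1.77) = 3.9%. The nine comparisons share the same pre-dose reading, so they are not independent. The chance of at least one qualifying reading is

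P = ∫ φ(z) [1 − (1 − Φ(z − 0.5/s))⁹] dz.

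The unrounded single-reading column below agrees with this integral. The rounded and two-reading columns are from simulation (400,000 draws).

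| Assumed s (°C) | Any of 9, unrounded | Any of 9, rounded to 0.1 °C | Two consecutive, unrounded | Two consecutive, rounded |
|---|---|---|---|---|
| 0.10 | 0.2% | 0.7% | <0.1% | <0.1% |
| 0.15 | 6% | 10% | 0.6% | 1.5% |
| 0.20 | 19% | 26% | 4% | 6% |
| 0.25 | 33% | 39% | 9% | 13% |

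**Step 3: relief set against clearance.** On a 0.1 °C scale, relief needs baseline − 0.5 or lower, and clearance needs 37.2 °C or lower for 24 hours.

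| Baseline (°C) | Relief needs | Cleared but not relieved if the lowest reading is | Fall |
|---|---|---|---|
| 37.3 | ≤ 36.8 | 36.9–37.2 | 0.1–0.4 |
| 37.4 | ≤ 36.9 | 37.0–37.2 | 0.2–0.4 |
| 37.5 | ≤ 37.0 | 37.1–37.2 | 0.3–0.4 |
| 37.6 | ≤ 37.1 | 37.2 | 0.4 |
| 37.7 | ≤ 37.2 | none | – |

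From 37.7 °C upward, clearance implies relief. At 37.6 °C the gap is a single value. This step needs no assumption about reading error.

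**Step 4: candidate repairs at a low fever.** Take a constant true temperature of 37.4 °C, s = 0.15 °C, unrounded readings, and a measured baseline of at least 37.3 °C.

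- Rule as written: about 8% false relief. This is above the 6% in Step 2 because patients are selected on a measured baseline that is high enough.
- Two consecutive readings that are either 0.5 °C down or below 37.3 °C: about 36%.
- Two consecutive readings 0.5 °C down, or a full clearance event (here, all nine readings below 37.3 °C): about 1%.

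The middle rule also does worse with rounding at a true 37.3 °C, where false relief rises from 16% to 61%.

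**The case against.** **The two outcomes are separate, and nothing says they are nested.** This is correct, and the low-grade patient who clears still counts in full under time to fever clearance and in the fever score of Table 4. A reader might infer that the definitions contradict each other or that the meaning of the endpoint is inverted. The document does not support that. Censoring some patients in a low-grade subset of unknown size does not reverse a treatment comparison. What stands is narrower: the expected order of relief and clearance breaks for those baselines.

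**The noise effect is assumed, not shown.** This is also fair. At a reading SD of 0.10 °C it is negligible. The model holds temperature flat for 24 hours, and the false events fall on all arms alike, so the harm is dilution and not a bias towards one arm. A material effect needs an SD of about 0.15 °C or more.

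**Any patient whose 0.5 °C fall would land below 37.3 °C might seem to be affected.** That would include 37.7 °C, but there every cleared patient has already fallen 0.5 °C. The range stops at 37.6 °C.

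**Confirmation rules usually belong in an analysis plan, which is not shown.** This has some force for the confirming reading and the reference temperature. It does not remove the point, because the article states the event rule, and the rule as stated censors some recovered patients.

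**Conclusion.** The point holds as a minor one.

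The cleared-but-not-relieved case follows from the protocol's own thresholds, assuming only readings to 0.1 °C. It is confined to baselines of 37.3–37.6 °C. How many patients this concerns cannot be computed, because no baseline temperature distribution is given. The possible loss of a later fall after 24 hours follows from the diary rule.

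The size of the noise problem depends wholly on the assumed reading error, from under 1% to 33–39% over SDs of 0.10–0.25 °C, with independent errors and a constant true temperature.

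The primary outcome and the sample size are untouched.

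**What to change.** Define time to fever relief as the time from first dosing to the earlier of:

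- (a) the first of two consecutive scheduled readings that are each at least 0.5 °C below the pre-dose reading;
- (b) the onset of fever clearance as the protocol already defines it, below 37.3 °C for 24 hours.

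Part (a) makes chance events much rarer and names the reference reading. Part (b) ensures that every cleared patient also counts as relieved. Two isolated readings below 37.3 °C should not serve as an alternative trigger, because they increase noise-only events at the lowest fevers (Step 4 of the working). Keep the single-reading definition as a sensitivity analysis.

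The cost is the wording of one secondary outcome. The first-day readings are already scheduled, and with recruitment still under way (Trial status) the change can be made before unblinding. There are two small downsides. Transient drops no longer count. After 24 hours, confirmation relies on the clearance rule, because readings below 37.3 °C may not be recorded.

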### Change in TCM symptom and sign scores

The TCM symptom scoring system used in the study follows the *Guidelines for Clinical Research of New Chinese Medicine* [24], in which all symptoms are graded (Table 4). The change in cumulative TCM symptom and sign scores is assessed by the percentage of symptom and sign scores reduction (PSSSR), which is calculated according to the following formula: PSSSR = (scores before treatment – scores after treatment)/scores before treatment*100%. A value greater than 50% is defined as clinically effective.

**Table 4 Tab4:** Symptom and sign scoring system

Symptom	Score			
Primary	None (0)	Mild (2)	Moderate (4)	Severe (6)
Fever	<37.3 °C	37.3–37.9 °C	38.0–38.4 °C	≥38.5 °C, <39.0 °C
Pharynx uncomfortable	–	Dry pharynx	Burning pharynx	Pharynx pain
Secondary	None (0)	Mild (1)	Moderate (2)	Severe (3)
Stuffy nose	–	Heavy sound	Sometimes	Sustained
Running nose	–	Occasionally	Sometimes	Sustained
Thirsty	–	No need for water	Sometimes need water	Need water frequently
Cough	–	Occasionally	Sometimes	Frequently
Headache	–	Occasionally, mild	Sustained, moderate	Heavy, can’t insist on work
Limb pain/soreness	–	Weak, uncomfortable	Painful	Terrible, can’t stretch freely
Cumulative symptom score	Primary symptom scores + secondary symptom scores			
Sign	None (0)	Mild (1)	Moderate (2)	Severe (3)
Pharyngeal hyperemia/swelling	–	Pharyngeal mucosa hyperemia	Pharyngeal mucosa, pharynx palatine arches and uvula hyperemia	Pharyngeal swelling and heavy secretion
Total score	All symptom scores + sign score			

– No symptom

